## Abstract

**Introduction:**

A wide range of water-related problems contribute to the global burden of disease. Despite the many plausible consequences for health and well-being, there is no validated tool to measure individual- or household-level water insecurity equivalently across varying cultural and ecological settings. Accordingly, we are developing the Household Water Insecurity Experiences (HWISE) Scale to measure household-level water insecurity in multiple contexts.

**Methods and analysis:**

After domain specification and item development, items were assessed for both content and face validity. Retained items are being asked in surveys in 28 sites globally in which water-related problems have been reported (eg, shortages, excess water and issues with quality), with a target of at least 250 participants from each site. Scale development will draw on analytic methods from both classical test and item response theories and include item reduction and factor structure identification. Scale evaluation will entail assessments of reliability, and predictive, convergent, and discriminant validity, as well as the assessment of differentiation between known groups.

**Ethics and dissemination:**

Study activities received necessary ethical approvals from institutional review bodies relevant to each site. We anticipate that the final HWISE Scale will be completed by late 2018 and made available through open-access publication. Associated findings will be disseminated to public health professionals, scientists, practitioners and policymakers through peer-reviewed journals, scientific presentations and meetings with various stakeholders. Measures to quantify household food insecurity have transformed policy, research and humanitarian aid efforts globally, and we expect that an analogous measure for household water insecurity will be similarly impactful.

Strengths and limitations of this studyThis study is based on rigorous, multidisciplinary formative research on water insecurity by anthropologists, geographers, nutritionists, statisticians and epidemiologists, among others.Data on household water insecurity experiences are being collected in 28 sites across four continents by local partners in widely varying ecological and cultural settings.Analytic methods from both classical test and item response theories will be used to develop and evaluate the eventual scale.The Household Water Insecurity Experiences Scale will be validated for assessing water insecurity in low-income and middle-income countries. Additional scale assessments necessary for validation in high-income countries are planned.

## Introduction

Water insecurity, the inability to ‘access and benefit from affordable, adequate, reliable and safe water for well being and a healthy life’,^1^ has manifold adverse effects on physical^2 3^ and psychosocial health^4 5^; undermines productivity^6^; triggers and perpetuates domestic, social and political tensions and conflicts^7 8^; and reinforces environmental and social inequities.^9^ Water insecurity has been shown to co-occur with food insecurity, malnutrition and communicable diseases and to produce syndemics, or systemically exacerbating epidemics,^10 11^ much like food insecurity and HIV.^12^ Furthermore, water insecurity is projected to worsen in many regions due to climate change and increased inequalities in resource distribution.^9^

However, we do not know how many households or individuals globally are affected by water insecurity. Estimates of available surface water derived from satellite imagery suggest that 4 billion people worldwide experience severe water scarcity for at least 1 month of every year,^13^ and this is likely an underestimation given issues with infrastructure and access. Additionally, chronic flooding^14^ and poor water quality^15^ mean that many more individuals are experiencing water insecurity. Currently, measures of water at the national, regional and community levels are used and are referred to as indicators of water scarcity, water poverty or water security.^16–19^ These measures do not capture the range and granularity of how households experience water insecurity, including factors such as perceptions of quality,^20^ instances of water excess^21^ or perceived consequences for psychosocial^4 5^ and physical health and well-being.^22^ Furthermore, while household-level scales to measure water insecurity have been developed for several sites, for example, in the USA,^23^ Bolivia,^4^ Uganda,^24^ Ethiopia^5^ and Kenya,^10^ their comparability, comprehensiveness and applicability to other sites have not been systematically investigated or validated.

As such, a comprehensive, validated scale to measure the experiences of household or individual water insecurity would enable researchers, practitioners and policymakers to: improve estimates of water insecurity prevalence, identify factors that shape this phenomenon, recognise direct consequences of water insecurity, understand how to more effectively distribute resources, evaluate the impacts and cost-effectiveness of interventions and monitor progress towards the Sustainable Development Goals.^25^ Indeed, in March 2018, the UN’s High-Level Panel on Water cited lack of data on water in many parts of the world as a major challenge, and the need for better data on water as one of nine priority actions.^26^ Given that measures of household food insecurity (eg, Latin American and Caribbean Food Security Scale,^27^ Household Food Insecurity Access Scale,^28^ Food Insecurity Experience Scale^29^) have proven vital to implementation and evaluation of policy and programmes,^30–32^ development of an analogous household water insecurity scale is overdue and urgently needed, particularly for assessing water insecurity in low-income and middle-income settings where household water problems tend to be most pronounced and frequent.

Therefore, our objective is to develop and validate the first household water insecurity scale with broad applicability across low- and middle-income settings. The Household Water Insecurity Experiences (HWISE, pronounced *H-wise*) Research Coordination Network (RCN) was formed to facilitate the multicountry, collaborative data collection process required to validate the planned tool (‘the HWISE Scale’). The HWISE RCN brings together a large team of anthropologists, geographers, public health practitioners, physicians, epidemiologists, statisticians, sociologists, nutritionists, inter alia, all of whom have experience with water insecurity, food insecurity and/or scale development across a wide array of settings (http://www.hwise.org).

## Methods and analysis

### Phase 1: item development

#### Domain specification

Specifying the domains for a scale is the first step in item development (table 1, 1.1).^33 34^ The boundary of the domain of water insecurity, that is, the underlying construct that the scale will attempt to measure, was based on extensive literature review^1^ and draws on the team’s expertise in water insecurity, for example.^4 8 23 35^ We define water insecurity as the condition where ‘affordability, reliability, adequacy, and safety [of water] is significantly reduced or unattainable so as to threaten or jeopardize well-being’.^1^

**Table 1 T1:** Overview of planned methods and analyses for the development of the HWISE Scale*

Scale development activity	Procedures
Phase 1: item development	
1.1 Domain specification	Literature review.
1.2 Item generation	Literature review and Delphi methodology.
1.3 Content validity	By target population: two styles of cognitive interviews were used in the first eight sites, building on Delphi methodology.
1.4 Face validity	Pretesting and debriefing with enumerators at each site.
Phase 2: scale development	
2.1 Data collection	Enumerator training and survey implementation.
2.2 Item reduction	We will drop items with cumulative missing cases >30% (ie, ‘don’t know’, ‘non-applicable’ or true missing responses) in any one site.
	We will assess the performance of each item’s variation with other items in the scale using a correlation matrix; items with very low (<0.30) interitem correlation coefficients and very low (<0.30) item-total correlation coefficients across multiple sites will be considered for deletion, as will items that misfit the model, that is, with residual correlations >0.20.
	Item reduction in Rasch paradigm: item severity and item discrimination test.
2.3 Identify factor structure	We will use factor analysis across multiple sites to test for factor structure; items with very low factor loadings (<0.30), split factor loadings (high factor loadings (>0.50) in two domains) and high residual variances will be considered for deletion.
2.4 Assess measurement equivalence	We will use multigroup confirmatory analysis (a form of measurement invariance) on data from multiple sites to test for exact invariance in the hypothetical scale; invariance will be assessed in terms of factor structure (configural model), factor loadings (matric model), mean intercepts (scalar model) and factor means (strict model).
	We will use confirmatory factor analysis alignment optimisation to estimate the group-specific factor means and variances of scale items across all sites; it assesses approximate invariance of scale items across multiple sites.
Phase 3: scale evaluation	
3.1 Score scale items	Finalised scale items will be used in their unweighted form as sum scores or in weighted form as factor scores.
3.2 Assess reliability (internal consistency) of scale items	We will use Cronbach’s alpha and the Rasch reliability statistic to test the internal consistency of the scale items within each site and aggregated across sites.
3.3 Assess scale validity	We will measure predictive, convergent and discriminant validity of the final scale items using criteria that were selected based on their strong theoretical relevance in the water insecurity literature; tests of water insecurity differences between ‘known groups’ will also be performed.

*Adapted from ref 34.

A best practice is to clearly articulate subdomains of the eventual scale, if they are known.^34 36^ Although some subdomains of water insecurity have been proposed,^1 5 11 37^ there is currently no consensus in the literature. Therefore, we will assess subdomains during the analytic phase.

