#### Item generation

Candidate scale items were identified deductively, based on an extensive literature review of items used in prior site-specific household water insecurity scales^1^ (table 1, 1.2). This includes team members’ prior work in *colonias* in the USA-Mexico boderlands^23^; a squatter settlement in Cochabamba, Bolivia^4^; in rural, periurban and urban households in Kenya^10^; and elsewhere, including rural areas in Ethiopia^5^ and Uganda.^24^ Initial items include experiences of water insecurity that have consequences for psychosocial and physical health, nutrition, impacts on livelihoods and household economy, and agriculture (online supplementary file 1).

10.1136/bmjopen-2018-023558.supp1Supplementary file 1

Each question is phrased to elicit experiences within the prior 4 weeks or month (ie, ‘In the last four weeks, how frequently have…’). This recall period was systematically determined using the Delphi method of consensus building with international and local experts in water insecurity, food insecurity and scale development and by comparing the responses in this recall period to a prospective daily recall of water insecurity experiences.^10^ Items were ordered by what we expected to be increasing severity of water insecurity across access, reliability, adequacy and safety. Response options are ‘never’ (0 times), ‘rarely’ (1–2 times), ‘sometimes’ (3–10 times), ‘often’ (11–20 times), ‘always’ (more than 20 times), ‘not applicable’, ‘don’t know’ or refused. Response intervals were also determined using the Delphi method.^10^

The initial set of 32 items is referred to as ‘Module Version 1’. This set of items was modified slightly in August 2017 (see ‘Mid-study Evaluations’ under Phase 3) based on feedback received from consortium members, survey implementers and other water security experts during a 3-day conference at Northwestern University. Modifications included slight rephrasing of 18 items to improve comprehension by participants and to elicit experiences related to water overabundance, two questions were added in an effort to capture cultural components of water and six items were eliminated for being too rare or idiosyncratic. The resultant set of 28 items is referred to as ‘Module Version 2’ (online supplementary file 1).

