#### Participant selection

To participate, individuals must be 16 or 18 years of age or older (depending on age of consent at each site), identify themselves to the interviewer as being knowledgeable about water acquisition and use within their households and consent to participate. Participants are not remunerated for participation in the survey.

The target sample size at each site is 250 individuals. We consider this sample size as the minimum needed for assessing the magnitude of correlation between the observed variables and associated factor(s) and obtaining a sample pattern that is stable and approximates the population pattern.^40^ If sites cannot achieve the target sample size, variation of estimated statistics will be reviewed to determine if the data can be included in the final validation of the scale.

The preferred sampling strategy for the study is random sampling of mutually exclusive and exhaustive categories of participants in areas of known high, moderate and low water insecurity. In standalone HWISE sites, participant selection follows a simple randomised or cluster-randomised sampling strategy (table 3). In several sites, however, the HWISE survey is administered as part of a larger ongoing project with a predetermined survey design (eg, in Singida, Tanzania: NCT02761876; Kahemba, Democratic Republic of Congo: NCT03157336), such that simple random sampling is not possible.

**Table 3 T3:** Overview of data collection activities at each HWISE study site

World Bank region	Site	Module Version	Implementing partners	Month(s) and year of data collection	Sample size	Female respondents, %	Season of data collection	Language(s) of data collection	Sampling strategy	Data collection method (software)	Details of larger study; supplementary data collected	IRB of record	Cognitive interviewing (Y/N)
Africa	Accra, Ghana	1	University of Miami, Delaware State University, Ghana Water Company and Northwestern University.	June 2017	229	78.2	Rainy season.	English.	Simple random.	Tablet (ODK).	Standalone.	University of Miami; Delaware University, reliant on Northwestern University and Ghana Water Company.	Yes
	Lagos, Nigeria	1	College of Medicine at the University of Lagos and Northwestern University.	June–August 2017	239	73.5	Rainy season.	English, Yoruba and Pidgin.	Multistage random.	Paper, entered into database (Enketo).	Standalone; adolescent menstrual hygiene.	Northwestern University & University of Lagos	Yes

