### Assess measurement equivalence

Measurement equivalence concerns the extent to which the psychometric properties of the observed indicators are generalisable across groups or over time.^52–55^ It holds ‘when a test measures a construct in the same way regardless of group membership and is violated when individuals from different groups respond to the test in a dissimilar manner’.^39^ A violation of equivalence implies our inability to make comparisons about the measurement and meaning of scale values across groups (eg, sites, cultures and languages).^39^ To determine measurement equivalence across sites using Module Versions 1 and 2, we will use multigroup confirmatory factor analysis and alignment optimisation.^56–58^

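### Cross-site equivalence is specified on loadings and mean intercepts although the items are five ordered categories of differing severity; on that footing, differences in site level alone can make identical items fail

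*Protocol article*

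**What the plan says.** Table 1, item 2.4 plans a multigroup confirmatory factor analysis "on data from multiple sites to test for exact invariance in the hypothetical scale". After the configural model, the parameters compared are "factor loadings (matric model), mean intercepts (scalar model", followed by factor means in the strict step; the definition of the strict step is not at issue here. Thresholds are not mentioned. The same item adds alignment optimisation, of which it says that "it assesses approximate invariance of scale items across multiple sites".

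The Item generation section gives each item five ordered answers: never (0 times), rarely (1–2 times), and then "sometimes’ (3–10 times), ‘often’ (11–20 times), ‘always’ (more than 20 times". Items were arranged by expected severity.

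The Sites section says that sites were sought for maximal heterogeneity, including in their problems with water. The target is 250 participants in each of 28 sites.

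On consequences, the section Assess measurement equivalence states: "A violation of equivalence implies our inability to make comparisons about the measurement and meaning of scale values across groups". The closing paragraph of the Validity section makes equivalent measurement across sites one criterion for including an item, and allows judgement about trade-offs. The Analytic strategy section names Mplus 8 and Stata 14 for the classical analyses. It does not state the estimator or the item type.

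**The concern.** The parameters named do not match the data described. A linear factor model gives each item one intercept and one constant slope on the latent trait. A five-category item anchored at zero has no constant slope: it is flat where nearly everyone answers never and steeper where answers spread over the categories. Its average slope in a site therefore depends on where the site lies on the trait. Items of different severity change by different factors, and a free factor variance in each site cannot absorb that. The metric test then responds to the level of the site as well as to the behaviour of the item.

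Cross-site comparability is the purpose of the scale. A false finding of non-equivalence would count against items that work, the severest ones most, and would weaken the claim that scores can be compared between sites.

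**Working it through.** The article gives no power, error rate or fit cut-off for this test, so there is no planned figure to reproduce.

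**Inputs from the article:** 28 sites; 250 per site (Table 3 sizes in the simulations); five ordered categories; items of differing severity; fewer than 20 items expected (12 used).

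**Assumptions:** standardised loading 0.75 (0.60 as sensitivity); the range across items of the share answering never; SD of site means 0.25 to 0.75 in within-site SD units; a CFI change of .01 as the conventional cut-off.

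**Step 1, the mechanism.** Take one cut, never versus any, with threshold τ and loading λ, identical in all sites. In a site with latent mean μ and SD 1, the average linear slope is λφ(τ − λμ). The ratio of slopes between sites at +m and −m is exp(2τλm). With λ = 0.75 and m = 0.5:
- 90% never, τ = 1.282: exp(2 × 1.282 × 0.75 × 0.5) = exp(0.961) = 2.61.
- 30% never, τ = −0.524: exp(2 × −0.524 × 0.75 × 0.5) = exp(−0.393) = 0.67.

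Identical items thus get slopes that change by different factors. For full five-category items with never ranging from .3 to .9, the fitted linear loadings in a +0.5 SD site against a −0.5 SD site have ratios of 2.56 (severest) and 1.20 (mildest).

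**Step 2, rejection of the metric step when all items are truly equivalent.** df = (12 − 1) × (28 − 1) = 297. Rejection is the probability that a noncentral chi-square on 297 df exceeds the central 95% point. For never .4–.8, loading 0.75 and site SD 0.5, the noncentrality is 241.2 and rejection is essentially 100%.

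| Share never across items | Loading | Site SD 0.25 | 0.50 | 0.75 | CFI drop at these SDs |
|---|---|---|---|---|---|
| .5–.7 | 0.75 | 17% | 77% | 99.7% | at most .004 |
| .4–.8 | 0.75 | 79% | 100% | 100% | .002 / .007 / .015 |
| .3–.9 | 0.75 | 99.9% | 100% | 100% | .004 / .016 / .032 |
| .4–.8 | 0.60 | 21% | 89% | 100% | .001 / .005 / .011 |
| .3–.9 | 0.60 | 53% | 100% | 100% | .003 / .012 / .024 |
| No floor, severity ±0.5 SD | 0.75 | 40% | 99.9% | 100% | .001 / .003 / .008 |

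With equal site means, or with all items equally severe, rejection is 5%. The scalar step is less affected: at site SD 0.5 and loading 0.75 it rejects 98% (never .3–.9) or 69% (.4–.8); at loading 0.60, 38% and 17%.

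**Step 3, finite samples at Table 3 sizes**, judged against critical values simulated under equal site means. Never .4–.8: 50% at site SD 0.25 and 100% at 0.5, with a CFI drop above .01 in 93% of runs at 0.5. Never .5–.7 at site SD 0.5: 93%, with a CFI drop above .01 in none. The finite-sample CFI drop for .4–.8 exceeds the population value of .007, so it should not be put down to site level alone.

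**Step 4, only two sites, 250 each.** One SD apart: 97% rejection for never .3–.9 (loading ratios 1.18 to 2.47), but 18% for .5–.7. At 0.5 SD apart, 18% to 38% for wider severity.

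**Step 5, the ordered-categorical alternative** (4 sites of 250, 6 items, 40 runs per setting). Linear metric df = 5 × 3 = 15; ordinal df for slopes and thresholds = 3 × (6 × 5 − 2) = 84.

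| Site means | Linear: mean chi-square, rejection | Ordinal: mean chi-square, rejection |
|---|---|---|
| all 0 | 18.2, 15% | 86.2, 2.5% |
| ±0.2, ±0.6 | 34.6, 78% | 85.2, 12.5% |
| ±0.3, ±0.9 | 61.4, 100% | 84.7, 5% |

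The linear test is not corrected here for non-normality, hence 15% with equal means. With 40 runs the standard error at a true 5% is √(0.05 × 0.95 / 40) = 3.4 points, so the ordinal rates are rough. Their mean chi-squares stay near 84 and show no trend with site spread.

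**The case against.** The linear model is an inference. The article names no estimator, intercepts is also a generic label for the scalar step, Mplus 8 can fit the ordinal model, and item type is a detail that an article may leave to its full analysis plan. This stands as a limit on what can be claimed. It does not clear the text, because the table does name the parameters, and for these items it names the wrong ones. If a categorical model was intended, the table misdescribes it.

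Three stronger readings are tempting, and the article does not support them:
- *That sites were chosen to run from low to high water insecurity.* The phrase "in areas of known high, moderate and low water insecurity" stands under Participant selection and describes the preferred sampling of participants. Sampling across levels within each site could even narrow the gaps between site means. The Sites section speaks of heterogeneity in region, infrastructure and kind of water problem. Differences in level are plausible, but their size is not given.
- *That the items sit at a floor.* No response distributions are reported, and six items were already dropped for Module Version 2 as too rare or idiosyncratic. A floor enlarges the artefact but is not needed for it, as the last row of the first table shows.
- *That items will fail and severe ones will be removed.* Item 2.4 has no pass mark and no deletion rule, alignment is also planned, and judgement can override any single criterion.

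The other planned analyses are no clear rescue. Alignment on the same linear loadings and intercepts should inherit the distortion (by reasoning; not simulated). The Rasch differential item functioning in the Validity section compares known groups such as water source, not sites.

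**Conclusion.** The point holds conditionally. The article states parameters of a linear model for ordered items of differing severity. If the analysis follows that wording and site means differ, items that are truly equivalent can fail the metric step, and less often the scalar step, because of site level. At an SD of site means of 0.5 and a loading of 0.75, false chi-square rejection across 28 sites is about 77% to 100%. At an SD of 0.25 it ranges from 17% to 99.9%. Judged by a CFI change of .01, the problem is small when items are of similar severity and material only when both severity and site spread are wide. Without differences in site means there is no artefact. Item distributions, loading and site spread are all assumptions.

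This should be corrected, because the article ties non-equivalence to an inability to compare sites and uses equivalence to select items. It does not show that the final scale would be wrong.

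**What to change.** In Table 1, item 2.4, replace mean intercepts with item thresholds. State that the multigroup confirmatory factor analysis treats the items as ordered-categorical in Mplus 8, with a configural model followed by equal loadings and thresholds. Where upper categories are sparse or empty in some sites, merge them in the same way in all sites. For alignment, use a categorical specification where feasible; otherwise report a never-versus-any alignment, modelled as categorical, as a sensitivity analysis beside the planned one.

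The cost is a change of wording and different model options in software already named; no data collection changes. Merging categories loses some information. Dichotomising loses considerably more, since it keeps only one of the four cut points between categories, and for that reason it should not replace the planned alignment.

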## Phase 2: scale development

### Data collection

#### Sites

Cross-sectional surveys were initially planned for six sites that would leverage investigators’ active research: Bangladesh, Brazil, Guatemala, Kenya, Nepal and Tajikistan; that is, they were selected out of convenience. Subsequently, 22 more were added because additional sites would allow us to test the instrument across more heterogeneous cultural and geographic settings (figure 1), permit an iterative analysis of the instrument (compared with ‘Mid-study evaluation’) and make a number of statistical analyses possible (table 2).^39^ These additional 22 sites were added by soliciting collaborators from professional networks across academic institutions as well as non-governmental and governmental organisations using convenience sampling. In selecting sites, we sought maximal heterogeneity in region of the world, infrastructure (eg, urban and rural, formal and informal settlements) and problems with water (eg, flooding, drought, chronic scarcity and intermittent supplies). We also considered cost and feasibility of timely implementation.

**Table 2 T2:** Characteristics of HWISE sites for scale development by region

World Bank region	Site (Module Version)	Primary sources of drinking water, %	Köppen climate classification at site (Köppen code)*	GNI per capita (USD)†	National income classification‡	Urbanicity of site
Africa	Accra, Ghana (1)	Bagged/sachet water, 86.0. Borehole/tubewell, 5.7. Other, 8.3.	Equatorial, winter dry (Aw).	1380	Lower middle income.	Urban
	Lagos, Nigeria (1)	Bagged/sachet water, 48.9. Borehole/tubewell, 34.7. Other, 16.4.	Equatorial, winter dry (Aw).	2450	Lower middle income.	Urban
	Kahemba, DRC (1)	Surface water, 99.7. Other, 0.3.	Equatorial, winter dry (Aw).	420	Low income.	Rural
	Bahir Dar, Ethiopia (1)	Unprotected dug well, 25.1. Rainwater collection, 20.9. Standpipe, 13.5. Surface water, 13.5. Protected dug well, 12.4. Unprotected spring, 10.0. Other, 4.6.	Warm temperature, winter dry, warm summer (Cwb).	660	Low income.	Rural
	Singida, Tanzania (1)	Standpipe, 48.6. Unprotected dug well, 17.4. Borehole/tubewell, 12.9. Other, 12.8. Unprotected spring, 8.3.	Equatorial, winter dry (Aw).	900	Low income.	Rural
	Lilongwe, Malawi (1)	Standpipe, 45.4. Piped water, 42.1. Other, 12.5.	Warm temperature, winter dry, hot summer (Cwa).	320	Low income.	Periurban

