### Identify factor structure

Factor analysis with data from multiple sites will be used to identify the optimal latent structure (table 1, 2.3). We will examine this structure for each site, comparing factor structures, magnitudes of factor loadings, eigenvalues for sample correlation matrices and global model fitness statistics. Items with low factor loadings (<0.30), split factor loadings and high residual variances (>0.50) will be considered for deletion.^34^

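### Table 1, item 2.4 defines the strict invariance step as equal factor means, which tests whether sites are equally water insecure; the step should constrain item residual variances

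*Protocol article*

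**What the plan says.** Table 1, item 2.4 plans multigroup confirmatory factor analysis "to test for exact invariance in the hypothetical scale". The first step concerns factor structure (configural). The other three are "factor loadings (matric model), mean intercepts (scalar model) and factor means (strict model"). The word printed as matric is evidently metric.

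The next row of the same item adds a second analysis, "alignment optimisation to estimate the group-specific factor means and variances of scale items across all sites", to assess approximate invariance.

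The section Assess measurement equivalence gives the concept: "Measurement equivalence concerns the extent to which the psychometric properties of the observed indicators are generalisable across groups or over time". It names multigroup factor analysis and alignment as the two tools and does not redefine the strict step.

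Residual variances appear only as an item screen, in Table 1, item 2.3 and in Identify factor structure: items with "high residual variances (>0.50) will be considered for deletion". The article describes no test that they are equal across sites.

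**The concern.** The first three steps constrain how the items relate to the factor: its structure, the loadings, the intercepts. The fourth constrains where each site sits on the factor. That level is what the scale exists to measure, so equality across sites is a claim about the populations and not about the instrument. A true difference in water insecurity between two sites breaks the constraint even when every item behaves identically in both.

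Two things are at stake. First, an analyst who follows the table fits the wrong constraint and may report real site differences as a lack of strict equivalence. Secondly, the constraint that belongs in this step, equal residual variances, is absent from the article's ladder. Residual variances determine how precise and reliable a score is in each site, and the plan uses unweighted sum scores and reports reliability both by site and aggregated.

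**Working it through.** **1. Comparison of the passages.**
- Assess measurement equivalence treats equivalence as a property of the indicators. A factor mean is a property of a site's population.
- The alignment row of item 2.4 estimates a separate factor mean for each site, so the means are expected to vary. The multigroup row of the same item makes their equality the final test of exact invariance.
- The section Sites states: "In selecting sites, we sought maximal heterogeneity in region of the world", and goes on to infrastructure and problems with water. Differing levels of water insecurity are therefore likely, though the text does not say that sites were chosen on level.

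**2. Size of the effect.** The article gives no test, alpha or power for this step, so there is no stated figure to reproduce. The following is an illustration.

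Inputs from the article: 28 sites (Abstract) and a target of 250 per site (Participant selection).

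Assumptions: items exactly invariant; chi-square difference test at alpha 0.05; score reliability *r* of 0.80 to 1.0; between-site SD of true factor means, *s*, in units of the within-site factor SD.

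Degrees of freedom = 28 − 1 = 27; critical value 40.11.

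Noncentrality = 28 × 250 × *s*² × *r* = 7000 × *s*² × *r*.

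| *s* | *r* | Noncentrality | Probability of rejecting equal means |
|---|---|---|---|
| 0.05 | 0.80 | 7000 × 0.0025 × 0.80 = 14.0 | 0.502 |
| 0.05 | 0.90 | 15.75 | 0.567 |
| 0.05 | 1.0 | 17.5 | 0.629 |
| 0.10 | 0.80 | 7000 × 0.01 × 0.80 = 56 | 0.9988 |
| 0.10 | 0.90 | 63 | 0.9997 |
| 0.10 | 1.0 | 70 | 0.9999 |
| 0.20 | 0.80 | 224 | 1.000 |
| 0.30 | 0.80 | 504 | 1.000 |

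**3. Simulation check.** One factor, 12 items, loadings 0.7, residual variance 0.51 in every site, 28 × 250 respondents, covariance treated as known, 1000 runs per setting. Measurement is identical across sites by construction.

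| *s* | Scalar step rejected | Equal-means step rejected |
|---|---|---|
| 0 | 6.1% | 4.0% |
| 0.05 | 3.9% | 59.2% |
| 0.10 | 5.3% | 100% |
| 0.20 | 4.9% | 100% |
| 0.30 | 4.2% | 100% |
| 0.50 | 4.5% | 100% |

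The scalar step holds close to its nominal 5% throughout. Only the equal-means step responds, and it responds to true site differences.

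**4. Sensitivity to the criterion.** Suppose the step is judged by the fall in the comparative fit index (CFI). In the same 12-item model the approximate fall is the noncentrality of the equal-means constraint divided by that of the independence model. The latter is 7000 × 5.552 = 38,864. The reliability implied by the model is 0.920.
- *s* = 0.10: 64.4 / 38,864 = 0.0017
- *s* = 0.20: 257.7 / 38,864 = 0.0066
- *s* = 0.30: 579.7 / 38,864 = 0.015

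Under an assumed cut-off of 0.01, the step would pass at 0.10 and 0.20 and fail at 0.30.

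**The case against.** The strongest defence is that little depends on this step. A reader might infer from the table that a perfectly equivalent scale would be rejected. The article does not support that. It attaches no decision rule to the strict step, and the closing paragraph of the Validity section expects items to meet the criteria imperfectly and leaves trade-offs to judgement. Nor does failure lead to dropping an item: that paragraph lists equivalence across sites as an inclusion criterion, but an equal-means constraint involves no item parameter and so points to no item. The loading and intercept steps are correctly specified, and alignment already lets the means vary. All of this stands and limits the harm.

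A reader might also infer that sum scores cannot be compared because residual variances are not tested. That goes too far. In the linear factor model the expected sum score at a given factor level depends on intercepts and loadings, which the scalar step covers. Residual variances affect precision and reliability, and reliability is at least examined site by site with Cronbach's alpha and the Rasch statistic. That is not a test of equality. The absence of such a test can be asserted only of this article, since a separate analysis plan may exist.

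It may also be said that the cell is a drafting slip, like matric beside it. Perhaps so, but it is the only definition of the ladder in the article and no other section corrects it.

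**Conclusion.** The point holds as an error in one step of the ladder. Equality of factor means is not strict invariance; it conflicts with the article's own definition of equivalence and with the alignment row beside it. Applied as written, it would report a failure of this step for a perfectly invariant scale whenever sites truly differ.

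How readily that happens depends on a criterion the article does not state. Near-certain rejection at a between-site SD of 0.10 rests on the assumed chi-square test, alpha 0.05 and full recruitment at 28 × 250. With an assumed CFI cut-off of 0.01, it would take a spread between 0.20 and 0.30 in the illustrative model. The direction of the error is the same under either criterion.

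The consequence is a misleading report on one of four steps and a missing check on residual variances. Rejection of the scale or of any item does not follow.

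**What to change.** In Table 1, item 2.4, make the strict model the one that adds equal item residual variances to the scalar model, in place of equal factor means. Leave factor means free across sites. Add a sentence saying that differences in site means are results, to be interpreted once scalar or approximate (alignment) invariance is supported, and are not evidence against equivalence. Correct matric to metric in the same edit.

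The cost is one table cell, one sentence and one changed model constraint in Mplus, with no new data. The change should be made before the invariance models are run.
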